## Populations for Analyses

11.3.1 Safety population

The safety population includes all enrolled participants who received ICG injection during pancreatectomy. All safety analyses in relation to the intervention will be done with this same population.

11.3.3 Efficacy evaluable population

The efficacy evaluable population includes all participants enrolled in this study who underwent pancreaticoduodenectomy or distal pancreatectomy, received ICG injection and had up to 30 days of postoperative follow-up for complications. Safety analyses for surgery will use the efficacy population.

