| **Secondary Objectives** | Evaluate the grade of leak via ISGPS classification and ICG metrics  Determine feasibility of intraoperative measurement of pancreatic perfusion using ICG and the SpyElite platform via a survey to be completed by OR staff.  Evaluate logistics of intraoperative perfusion measurement for staff and operating room using a survey. |
| **Primary Endpoint** | Incidence of biochemical leak or fistula after pancreatectomy defined by definitions of the ISGPS criteria |
|  | |
| **Key Inclusion Criteria** | Patients undergoing open pancreaticoduodenectomy or distal pancreatectomy for any diagnosis will be evaluated for inclusion. |
| **Key Exclusion Criteria** | Development of intra- or post-operative occurrences known to be associated with postoperative pancreatic fistula including hemorrhage, intraoperative blood transfusion, sustained postoperative hypotension requiring vasopressor support, unexpected ICU transfer, initiation of ACLS protocols will be excluded.  Patients with adverse reactions or allergies to indocyanine green will be excluded. History of prior pancreatectomy, prior severe pancreatitis, history of chronic pancreatitits, visceral vascular abnormalities, severe atherosclerosis, planned vascular reconstruction, hepatic insufficiency, liver fibrosis or cirrhosis will be excluded. |
| **Number of Participants** | *n* = 50 patients; anticipate screening *n =* 75 individuals. |
| **Duration of Therapy** | One 5.0 mg IV dose of indocyanine green, intraoperatively, with repeat intraoperative dosing up to maximum 2mg/kg |
| **Duration of Follow Up** | Thirty (30) days. |
|  | |
| **Description of Study Intervention** | Study participants will undergo one intraoperative measurement of pancreatic remnant perfusion. This involves intravenous administration of indocyanine green dye during their operation followed by immediate near-infrared perfusion measurement using the Stryker SpyElite camera, targeted at the organ of interest prior to drug administration. The intervention is expected to take five minutes total. |
|  | |

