## Participant Exclusion Criteria

An individual who meets any of the following criteria will be excluded from participation in this study:

1. Patients with previous history of adverse reaction to contraste dye, ICG or components of the dye
2. Prior pancreatectomy
3. Known diagnosis of hepatic insufficiency, hepatitis, liver fibrosis or cirrhosis, or chronic pancreatitis
4. Because this study focuses on hypoperfusion, patients will be excluded if in postoperative day 3-5 had any of the following: persistent SBP <90 mmHg unresponsive to 1L crystalloid, unexpected ICU transfer, blood transfusion of >2 units intraoperatively or 1 postoperatively, vasopressor treatment or ACLS protocol initiation
5. Organ failure, anuria or NSQIP-identified complication will be reviewed by PI and attending surgeon and excluded
6. Patients that require arterial reconstruction as part of their procedures

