## Participant Discontinuation or Withdrawal

Participants are free to withdraw consent and discontinue participation in the study at any time and without prejudice to further treatment. If a participant no longer wants to receive investigational product, but is willing to come for follow-up appointments, the participant’s request should be honored, if possible.

If a participant withdraws consent, they should be asked to specify if they are withdrawing consent to all further participation in the study, including any further follow up (e.g., survival contact telephone calls) or if they are choosing to withdraw only from further study intervention, meaning that further follow-up and data collection about their disease and health status is allowable. The participant should also be asked about their consent to the future use of their study-generated data and any biological samples, as applicable.

No further participant contact should be made if the participant withdraws consent for participation in the study. Information about the reason(s) for discontinuation and collection of any new or ongoing AEs should be collected at the time the participant withdraws consent.

A participant may also be withdrawn from the study by the Sponsor/Sponsor-Investigator, Investigator, local IRB, or regulatory authorities.

Reasons for a participant to discontinue the study may include the following:

• Participant dies or is lost to follow-up

• Participant withdraws consent for any further participation

• The end of study is reached

• Pregnancy

• Significant study intervention non-compliance

• If any clinical adverse event (AE), laboratory abnormality, or other medical condition or situation occurs such that continued participation in the study would not be in the best interest of the participant

• Disease progression which requires discontinuation of the study intervention

• If the participant meets an exclusion criterion (either newly developed or not previously recognized) that precludes further study participation

In the event of a pregnancy, the study treatment will not be administered. Refer to Section 10.6.5 regarding reporting of pregnancy. Participants who withdraw or discontinue after receiving study intervention count towards the enrollment total.

- - 1. Handling Participant Discontinuation from Study

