## Early Termination or End of Treatment Visit

Any participant who undergoes early termination will undergo end of study visits depending on their progress in the protocol. Participants who have not received ICG injection are not considered enrolled, will not require a follow up visit and will be treated per standard of care. Participants undergoing termination following pancreatectomy will have an end of study visit at the time of their regular post-op visit and will be cared for per the standard of care.

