## Sample Size Determination

This primary objective of study is to detect the difference in leak rates between normal and reduced ICG perfusion group. Since there are no existing data of ICG perfusion in the pancreas, the sample size calculation was not based on the hypothesis but we provided the detectable difference between two groups. Anticipating the balanced number between two groups, our sample size of 50 will have 80% power to detect at least 25% difference in leaks rate between two group assuming 20% leak rate for normal ICG perfusion group.

We consider a liberal exclusion of 30% due to multiple and complex postoperative factors known to be associated with leaks. We anticipate screening 75 patients and enrolling 50.

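### Surgical safety is assigned to the efficacy population, from which patients may be removed because they had a surgical complication; it should use the safety population

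*Protocol*

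**What the plan says.** Populations for Analyses defines two sets. Under 11.3.1, "The safety population includes all enrolled participants who received ICG injection during pancreatectomy", and that set serves safety analyses relating to the intervention. Under 11.3.3, the efficacy evaluable set is enrolled participants who had one of the two resections, were injected, and were followed for as much as 30 days. That paragraph ends: "Safety analyses for surgery will use the efficacy population". The Safety Analyses section tabulates AEs and SAEs in the safety set.

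The exclusions that matter are in three places:

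- Participant Exclusion Criteria, item 4: "patients will be excluded if in postoperative day 3-5 had any of the following". The list is persistent hypotension, unexpected ICU transfer, transfusion above set limits, vasopressor treatment and ACLS.
- Participant Exclusion Criteria, item 5: "Organ failure, anuria or NSQIP-identified complication will be reviewed by PI and attending surgeon and excluded".
- Synopsis, Key Exclusion Criteria, with no day window: "sustained postoperative hypotension requiring vasopressor support, unexpected ICU transfer, initiation of ACLS protocols will be excluded".

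Enrollment Procedures treats a patient as enrolled once the study intervention has been performed. Early Termination or End of Treatment Visit agrees: "Participants who have not received ICG injection are not considered enrolled". Participant Discontinuation or Withdrawal lists among possible reasons to discontinue: "If the participant meets an exclusion criterion (either newly developed or not previously recognized) that precludes further study participation". Sample Size Determination adds: "We consider a liberal exclusion of 30% due to multiple and complex postoperative factors known to be associated with leaks".

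**The concern.** A complication rate should be computed in a set whose membership does not depend on having had the complication. Here the set named for surgical safety is the one to which the postoperative exclusions would naturally apply, and those exclusions are surgical complications. NSQIP makes the overlap plain: it supplies the 30-day complication data (Follow-up; section 13.1.3), and an NSQIP-identified complication is also an item 5 trigger.

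If the exclusions are applied, the protocol yields two safety summaries of the same operations on different denominators, and the surgical one has lost patients because of their outcome. Anyone setting that rate beside the 47% morbidity quoted in the background for distal pancreatectomy would think the operations safer than they were.

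**Working it through.** **Does the exclusion fall on patients already in the sets?** Enrolment is fixed at injection, during surgery. ICU transfer, vasopressor treatment, ACLS or organ failure after the operation therefore arises in someone already enrolled and injected. Intraoperative transfusion may come before or after injection.

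**Does the exclusion reach the efficacy set?** The definition in 11.3.3 does not mention items 4 and 5. Item 4 gives its reason as the study's focus on hypoperfusion, so its purpose is to keep other causes of leak out of the perfusion analysis. It can do that only by removing patients from the efficacy set. 11.3.3 makes no exception for surgical safety.

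**The plan's own figure.** The protocol expects to screen 75 to enrol 50, with 30% excluded. Inflating 50 gives 50/0.70 = 71.4, or 72 patients; 75 × 0.70 = 52.5; and 25/75 = 33.3%. The stated 75 is not exactly reproduced, but it is close and the gap does not affect this point. The text attributes the 30% to postoperative factors, yet the screened-to-enrolled arithmetic places the loss before injection. The share falling after injection is therefore unknown.

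**Illustration.** Inputs:

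- 50 patients remain evaluable.
- Total excluded = 50/0.70 − 50 = 21.4.
- The post-injection share is assumed to be 100%, 50% or 25%, giving x = 21, 11 or 5 after rounding.
- True morbidity m = 47%, the background figure for distal pancreatectomy, assumed for all patients.
- Every excluded patient counts as a complication (assumed).

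Rate shown in the efficacy set = [m(50 + x) − x]/50. Understatement = x(1 − m)/50.

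| Post-injection share | x | Injected | Missing | Rate shown | Understatement (points) |
|---|---|---|---|---|---|
| 100% | 21 | 71 | 29.6% | 24.7% | 22.3 |
| 50% | 11 | 61 | 18.0% | 35.3% | 11.7 |
| 25% | 5 | 55 | 9.1% | 41.7% | 5.3 |
| 0% | 0 | 50 | 0% | 47% | 0 |

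First row: (0.47 × 71 − 21)/50 = 12.37/50 = 24.7%.

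For m between 40% and 60% (assumed range), the understatement is 25.2 to 16.8 points, 13.2 to 8.8 points, or 6.0 to 4.0 points for the three non-zero shares.

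If 50 is instead the number injected, with no replacement, then x = 15, 8 or 4 and the rate shown is (0.47 × 50 − x)/(50 − x) = 24.3%, 36.9% or 42.4%.

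**The case against.** The strongest reply is that 11.3.3, read literally, removes nobody for a complication. A patient sent to ICU on day 4 was enrolled, resected, injected and followed, and so meets every term. Both sets are defined as enrolled patients who were injected, so one rule applied to both gives matching tables. The discontinuation section only lists possible reasons, and it counts those who leave after the intervention toward the enrollment total. This stands as far as it goes: a reader might infer that the protocol certainly understates complications and that the two summaries cannot agree, and the text does not establish either. Both follow only if the exclusions are applied to the efficacy set and not to the safety set. But the literal reading leaves item 4 with no effect on the analysis it was written to protect, and it makes the separate assignment of surgical safety nearly pointless.

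A reader might also take the full 30% as lost after injection. The 75-to-50 accrual statement does not support that.

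Nor should one infer that all complications disappear. Item 4 has a day 3-5 window, item 5 depends on review, and item 5 cannot mean every NSQIP complication, because fistula, part of the primary endpoint, is collected through NSQIP (section 13.1.3).

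Finally, the stakes are limited. No separate surgical-safety endpoint, table or decision rule is described, and events of grade 3 or higher are recorded whatever their cause and tabulated in the safety set.

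**Conclusion.** The point holds in conditional form. The protocol itself fixes the population for surgical safety, and it chose the set exposed to exclusion on the outcome. If items 4 and 5 are applied to that set, the direction is certain: the surgical complication rate is too low and can differ from the AE and SAE tables. The size cannot be settled from the protocol. It is zero if no exclusion follows injection, and the percentages above are illustrations resting on an assumed post-injection share, an assumed morbidity, and the assumption that every excluded patient had a complication. Safety data as a whole are not lost. Severity is minor to moderate.

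**What to change.** Change the last sentence of 11.3.3 so that surgical safety analyses use the safety population. In 11.3.1, state that this population keeps every participant who received ICG, including anyone who later meets exclusion item 4 or 5. Whether those items should apply to the perfusion-leak analysis is a separate question, and this change does not depend on the answer.

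The cost is wording in two places. The 30-day NSQIP outcomes and grade 3 or higher events are already collected. The one downside is that the reported surgical complication rate may be higher. If excluded patients would have been kept anyway, the change alters almost nothing; if they would have been dropped, it removes the bias.

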## Description of Statistical Methods

- - 1. General Approach

Descriptive statistics will be used to summarize patients’ baseline characteristics and baseline disease characteristics. This information will be presented with percentages, means with standard deviations median and range as suitable. Inferential tests will use a null-hypothesis significance testing of <0.05.

- - 1. Analysis of Primary Endpoint(s)

*11.4.2 Primary endpoint – Leak rate*

We will assess the association between ICG perfusion and leaks using a chi-square test. Logistic regression analysis will be further utilized to evaluate covariates influencing the presence/absence of leaks, with specific attention to the predictive value of percent maximum perfusion metrics and time to maximum metrics at the set timepoints in the protocol. Refer to Sections 3.1 for additional information

- - 1. Analysis Of The Secondary Endpoint(S)

*11.4.3.1 Secondary endpoint –*

We will use descriptive statistics to summerize the grade of leasks and ICG metrics.

*11.4.3.2 Secondary endpoint – ICG logistics*

The results of the survey to be applied to surgeons and other OR staff will be summerized using a descriptive statistics.

- - 1. Safety Analyses

Adverse events will be tabulated by the Medical Dictionary for Regulatory Activities (MedDRA Version 21.1) preferred term and system organ class. The severity of the AE will be assessed by National Cancer Institute (NCI) Common Terminology Criteria for Adverse Events (CTCAE) version 5.0. Using the safety analysis set, descriptive statistics will be used to summarize all on-study AEs, grade 3-4 AEs, treatment-related AEs, grade 3-4 treatment-related AEs, SAEs, treatment-related SAEs, and AEs leading to study therapy discontinuation. Grade 3-4 laboratory abnormalities will be summarized using worst grade NCI CTCAE v5.0 criteria.

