We will use a cutoff of 60% of the maximum ICG uptake to consider cut edge as poorly perfused. (100% measured 4-6 cm from the cut edge of the pancreas point 5 and 6 in the figure below). Additionally, to compare with non-pathologic gastrointestinal tissue perfusion, ICG uptake metrics will be captured from the gastric body.

[figure not shown]

At the completion of the proposed study, the expected outcomes are to have evaluated the safety and efficacy of intra-operative ICG administration in the assessment of pancreatic perfusion at the cut edge.

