## Name of Study Intervention

- - 1. Study Intervention Description

**Indocyanine green**: ICG is an FDA-approved intravenous drug that binds albumin and when detected using near-infrared imaging performs well as a marker of blood flow and oxygenation.^26^ When applied intravenously, ICG travels to tissues by arteries. ICG has been used for more than 50 years. ^19^ Since then, studies of ICG both in the lab and in clinical trials, have shown promising results of its use in different surgical procedures. ICG has an excellent safety profile and adds little to no risk to patients undergoing surgery.^23, 24^

Study Device information is detailed in section 6.2, but briefly includes use of the Stryker Spy+ Elite platform. The Stryker Spy+ Elite is an FDA approved imaging system for intraoperative acquisition of near-infrared images and measurement of ICG perfusion kinetics and metrics. ICG uptake data will be measured immediately before reconstruction in the case of pancreaticoduodenectomies and for distal pancreatectomies, during visual inspection of right upper quadrant prior to surgical closure.

- - 1. Acquisition

ICG for Injection is on OHSU Pharmacy Formulary and comes as a single-patient vial of 25mg of lyophilized drug, which is then reconstituted with 10mL of sterile injectable saline.

- - 1. Formulation, Appearance, Packaging and Labeling

ICG is an FDA approved drug supplied as a sterile, lyophilized green powder containing 25 mg of indocyanine green with no more than 5 % sodium iodide. It is packaged with an Aqueous Solvent consisting of Sterile Water for Injection used to dissolve the indocyanine green. ICG is to be administered intravenously.

- - 1. Product Storage and Stability

ICG should be stored at 15° to 25° C.

ICG should be used within 6 hours after it is prepared.

- - 1. Compatibility

ICG should only be prepared with the included aqueous solvent.

- - 1. Handling

FDA data states that ICG is unstable in aqueous solution and must be used within 6 hours. However, the dye is stable in plasma and whole blood so that samples obtained in discontinuous sampling techniques may be read hours later. Sterile techniques should be used in handling the dye solution as well as in the performance of the dilution curves.

- - 1. Preparation

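### The primary test is an unadjusted chi-square on an unsupported 60% split, pooled over two operations; the logistic model already planned, with operation as covariate, should be primary

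*Protocol*

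**What the plan says.** Under Description of Statistical Methods, the analysis of the primary endpoint reads: "We will assess the association between ICG perfusion and leaks using a chi-square test". Tests are at the 0.05 level ("Inferential tests will use a null-hypothesis significance testing of <0.05"); sidedness is not given. The Sample Size Determination section frames the comparison as normal against reduced perfusion, and Description of the Study Design supplies the split: "We will use a cutoff of 60% of the maximum ICG uptake to consider cut edge as poorly perfused". The 100% reference is the same patient's pancreas 4 to 6 cm from the cut edge.

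The inclusion criteria admit open pancreaticoduodenectomy and distal pancreatectomy. Uptake is "measured immediately before reconstruction in the case of pancreaticoduodenectomies and for distal pancreatectomies, during visual inspection of right upper quadrant" before closure. No stratification or adjustment by operation is stated for the primary test.

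The same paragraph on the primary endpoint then plans logistic regression as a further analysis of covariates related to leak, with particular attention to percent-maximum and time-to-maximum metrics. It does not name the covariates.

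**The concern.** Two features of the primary test are weak.

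**The cutoff.** Percent-of-maximum uptake is continuous, and cutting it discards information unless risk really changes at the cut. The protocol gives no basis for 60%; it says itself "Since there are no existing data of ICG perfusion in the pancreas". The same gap undermines the even split that the power statement needs ("Anticipating the balanced number between two groups").

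**The pooling.** One operation removes the head of the gland and the other the far end, so both the cut edge and the reference tissue differ. Measurement comes before reconstruction in one and before closure in the other. The Background places leaks typically at the join of pancreas and bowel, and gives a leak rate of around 30% for distal resection. If operation is related to both measured perfusion and leak, a pooled two-by-two table can create an association that is not there or hide one that is.

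At stake is the trial's main result: whether reduced perfusion goes with leak, which is meant to justify a later trial of modifying perfusion.

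**Working it through.** **1. The plan's own figure.** The claim is "our sample size of 50 will have 80% power to detect at least 25% difference in leaks rate between two group". It rests on equal groups and a 20% leak rate under normal perfusion. So n = 25 per group, 20% against 45%, alpha 0.05, taken as two-sided. With mean rate 0.325:

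- SE under the null = √(2 × 0.325 × 0.675 / 25) = 0.1325
- SE under the alternative = √((0.20 × 0.80 + 0.45 × 0.55) / 25) = 0.1277
- Power = Φ((0.25 − 1.96 × 0.1325) / 0.1277) = Φ(−0.076) = 47%

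Exact enumeration gives 49% for Pearson chi-square and 36% for the Yates or Fisher versions. One-sided power is 60–61%. The stated 80% does not reproduce, so the comparison below starts from about 47–49%.

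**2. Information lost by cutting.** For a normal predictor, the asymptotic efficiency of a cut with a fraction p below it is φ(z_p)² / [p(1 − p)]: 0.64 at the median, 0.58 at 30% below and 0.49 at 20% below.

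**3. Power at N = 50.** The protocol gives neither the distribution of uptake nor its relation to leak, so both are assumed. Each scenario is calibrated to leak rates of 20% and 45% on the two sides of the cutoff, with 4,000 to 20,000 simulated trials. The logistic model contains continuous uptake and operation.

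| Assumed truth | Chi-square | Logistic, LR test | Logistic, Wald test |
|---|---|---|---|
| Normal, log-odds linear, half below | 48% | 67% | 62% |
| Normal, log-odds linear, 30% below | 44–45% | 62% | 56–57% |
| Uniform, log-odds linear, 30% below | 44% | 59% | 54% |
| Step at the cutoff, half below | 47–48% | 34% | 29–30% |
| Step at the cutoff, 30% below | 44% | 31% | 27% |

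A second simulation gave 46% against 66% (smooth, half below), 46% against 61% (smooth, 30% below) and 47% against 36% (step at the cutoff). With no effect, rejection was 4.6% for chi-square, 5.4% for the LR test and 3.8% for the Wald test, so the LR gain is not bought with a materially inflated error rate.

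**4. A step in the wrong place.** If risk steps at the median but the cutoff falls at the 30th percentile, power is 25% for chi-square and 36% for the logistic model. With the cutoff at the 20th percentile it is 17% against 35%. With a step at the 30th percentile and the cutoff at the median it is 21% against 30%. In these cases chi-square wins only when the cutoff is close to right.

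**5. False association through operation.** Illustration with no true effect: equal numbers of each operation, and hypoperfusion in 30% of one and 70% of the other.

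- Leak rates 20% and 30%: reduced group 0.3 × 20 + 0.7 × 30 = 27%; normal group 0.7 × 20 + 0.3 × 30 = 23%; spurious difference 4 points.
- Leak rates 10% and 40%: 0.3 × 10 + 0.7 × 40 = 31% against 0.7 × 10 + 0.3 × 40 = 19%; spurious difference 12 points.

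Under assumptions of this kind the unadjusted chi-square rejects about 6% to 16% of the time, against about 5% when stratified by operation. Where operation is unrelated to perfusion, stratifying costs 1 to 2 points of power. In the logistic model the operation term then costs almost nothing (67.6% without it, 67.4% with it).

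**The case against.** The strongest defence is that the chosen test is valid and coherent. With no effect and no confounding it holds its level. A prespecified cutoff with a matching two-group test agrees with the sample-size section, and the stated aim is preliminary data. If risk does step at 60%, the form in which the protocol casts the question, chi-square is the better test. All of this stands, and it is why the 60% comparison should be kept.

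Three stronger readings are tempting and are not supported:

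- **That the plan ignores the continuous measure.** It does not. The logistic analysis of percent-maximum metrics is already there; what is open is its rank and its adjustment for operation. A covariate list is commonly left to the SAP, so its absence alone is no finding.
- **That the change yields a fixed 17 to 19 points of power.** That size needs a roughly normal metric, a log-odds linear in uptake and a likelihood-ratio test.
- **That operation confounds the result and adjustment removes this.** The documents give no separate leak rate for pancreaticoduodenectomy and no perfusion by operation. Expressing uptake relative to each patient's own gland may also lessen the effect of different measurement moments. The leak and hypoperfusion rates in step 5 are illustrations, and a single covariate deals with operation only as far as the model is right.

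**Conclusion.** The point holds as a should-fix matter of analysis choice, not as an error that invalidates the test. The protocol fixes an unadjusted test on a cutoff without supporting pancreatic data, pooled over two operations that differ in remnant and in timing of measurement.

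Promoting the continuous, operation-adjusted model gains up to about 19 points of power under a smooth dose-response, or about 9 to 15 with a uniform metric or a Wald test. It loses about 11 to 18 points if risk truly steps at 60%. The case for stratifying by operation is firmer because it does not depend on the shape of that relation: 1 to 2 points of power buys protection against a type I error of about 6% to 16% under the assumed differences.

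All figures assume a two-sided test and N = 50; those with an operation term also assume about equal numbers of the two operations. Even the favourable balanced case reaches only about 67%, so the incorrect 80% power statement needs its own correction.

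**What to change.** - **Primary:** logistic regression of any leak on continuous cut-edge percent-of-maximum uptake, with operation type as the only covariate, tested by likelihood ratio at two-sided 0.05. At 20% and 45% in balanced groups about 16 leaks are expected (25 × 0.20 + 25 × 0.45 = 16.25), which suits a two-term model but not an open-ended one.
- **Key secondary:** the 60% comparison, stratified by operation (Cochran-Mantel-Haenszel).
- **Exploratory:** time-to-maximum and the other sampling points.
- **At minimum,** if the 60% comparison stays primary, stratify it by operation.

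The cost is a change of wording and trivial analysis work. The model is already planned and operation is known for every patient, so no new data are needed. The price is reliance on a roughly monotone relation on the log-odds scale, which can be checked, and the loss of power given above if 60% is a true threshold.
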